## Abstract

**Background:**

Women with chronic medical conditions, such as diabetes and hypertension, have a higher risk of pregnancy-related complications compared with women without medical conditions and should be offered contraception if desired. Although evidence based guidelines for contraceptive selection in the presence of medical conditions are available via the United States Medical Eligibility Criteria (US MEC), these guidelines are underutilized. Research also supports the use of decision tools to promote shared decision making between patients and providers during contraceptive counseling.

**Objective:**

The overall goal of the *MiHealth, MiChoice* project is to design and implement a theory-driven, Web-based tool that incorporates the US MEC (provider-level intervention) within the vehicle of a contraceptive decision tool for women with chronic medical conditions (patient-level intervention) in community-based primary care settings (practice-level intervention). This will be a 3-phase study that includes a predesign phase, a design phase, and a testing phase in a randomized controlled trial. This study protocol describes phase 1 and aim 1, which is to determine patient-, provider-, and practice-level factors that are relevant to the design and implementation of the contraceptive decision tool.

**Methods:**

This is a mixed methods implementation study. To customize the delivery of the US MEC in the decision tool, we selected high-priority constructs from the Consolidated Framework for Implementation Research and the Theoretical Domains Framework to drive data collection and analysis at the practice and provider level, respectively. A conceptual model that incorporates constructs from the transtheoretical model and the health beliefs model undergirds patient-level data collection and analysis and will inform customization of the decision tool for this population. We will recruit 6 community-based primary care practices and conduct quantitative surveys and semistructured qualitative interviews with women who have chronic medical conditions, their primary care providers (PCPs), and clinic staff, as well as field observations of practice activities. Quantitative survey data will be summarized with simple descriptive statistics and relationships between participant characteristics and contraceptive recommendations (for PCPs), and current contraceptive use (for patients) will be examined using Fisher exact test. We will conduct thematic analysis of qualitative data from interviews and field observations. The integration of data will occur by comparing, contrasting, and synthesizing qualitative and quantitative findings to inform the future development and implementation of the intervention.

**Results:**

We are currently enrolling practices and anticipate study completion in 15 months.

**Conclusions:**

This protocol describes the first phase of a multiphase mixed methods study to develop and implement a Web-based decision tool that is customized to meet the needs of women with chronic medical conditions in primary care settings. Study findings will promote contraceptive counseling via shared decision making and reflect evidence-based guidelines for contraceptive selection.

**Trial Registration:**

ClinicalTrials.gov NCT03153644; https://clinicaltrials.gov/ct2/show/NCT03153644 (Archived by WebCite at http://www.webcitation.org/6yUkA5lK8)

## Introduction

### Quality Gaps in Contraceptive Care

Access to family planning services to prevent unintended pregnancies is one of the leading health indicators for Healthy People 2020 [1]. Unintended pregnancies account for half of all US pregnancies [2] and are associated with adverse outcomes for women and children, such as maternal depression and low birth weight, respectively [3,4]. In 2008, US expenditures for live births resulting from unintended pregnancies were US $12.5 billion [5]. In 2014, the Centers for Disease Control and Prevention (CDC) and the US Office of Population Affairs jointly recommended an increase in the volume and quality of family planning services across all health care sectors, including primary care, to address this unmet public health need [6]. The Office of Population Affairs subsequently released contraceptive quality measures that assess the percentage of reproductive-aged fertile women who are provided moderately effective and highly effective contraceptive methods [7]. The National Quality Forum formally endorsed these measures in 2017, and the development of a patient-reported measure of contraceptive care is in progress [7]. There is a timely and critical need to disseminate and implement evidence-based interventions to meet these contraceptive quality measures and improve reproductive health outcomes.

### Implications for Women With Chronic Medical Conditions

Women with chronic medical conditions (eg, diabetes and hypertension) have a higher rate of pregnancy-related complications [8-11] and death compared with women without these conditions [12,13]. The most prevalent chronic medical conditions (hereafter called “chronic conditions”) among reproductive-age women have risen over the last 10 years and include obesity (24.7%), asthma (16.2%), high cholesterol (13%), hypertension (10%), and diabetes (2.9%) [14]. Expanded definitions of chronic conditions that include psychiatric conditions estimate that women with chronic conditions comprise up to 45% of reproductive age women seen in primary care [15,16]. Studies have raised concerns that adult women with chronic conditions are at greater risk for unplanned pregnancy [17] as they are more likely to not use any contraceptive method, underutilize the most effective methods, and rely upon the least effective methods compared with the general population of reproductive-aged women [18-21]. Women with chronic conditions are often prescribed medications that can cause fetal defects [22,23], and those who do not desire pregnancy should be offered contraceptive options. Contraceptive counseling should include an explanation of potential beneficial or adverse impact of a method on their conditions and interactions with ongoing drug therapy.

### Missed Opportunities and Barriers to Contraceptive Care in Primary Care

Women with chronic conditions most frequently see primary care providers (PCPs) for their health management [24]; these visits are windows of opportunity to address contraception within the context of ongoing medical care [25]. PCPs are well situated to address the contraceptive needs of women with chronic conditions, but the time constraints of office visits and incomplete provider knowledge are commonly cited barriers to doing so [26-28]. Although family planning is a required part of training for most PCPs, contraceptive knowledge is lower among PCPs compared with obstetrics and gynecology providers [27,28]; this is not surprising given the greater intensity of training and exposure to women’s health care among obstetrics and gynecology providers.

### Implementation of Evidence-Based Contraceptive Guidelines From the Centers for Disease Control and Prevention

In 2010, the CDC released the United States Medical Eligibility Criteria (US MEC), which was adapted directly from the World Health Organization’s MEC to meet the unique needs of US patients. The US MEC provides guidance to clinicians regarding the selection of contraceptive methods in the presence of specific chronic conditions (eg, seizures) and personal characteristics (eg, age) [29] and is revised on a continual basis. In 2011, the American Congress of Obstetricians and Gynecologists formally endorsed use of the US MEC for “clinicians providing family planning services for women, especially women with chronic conditions” [30] as an effort to promote national-level dissemination and implementation of evidence-based contraceptive practices. However, there is a significant gap between the US MEC and reported clinical recommendations, particularly with respect to the intrauterine device and the implant—the most effective long-acting reversible contraceptives (LARC) [26,28,31-34]. LARC methods are estrogen-free and safe for the vast majority of women, including those with conditions that may preclude the use of estrogen (eg, cardiac disease) [35-37]. It is critical to correct PCP misconceptions about LARC eligibility so that they do not unnecessarily prevent LARC use among women with chronic conditions, who are otherwise appropriate candidates [36], thus placing them at risk for unintended pregnancy.

### Evidence-Based Contraceptive Counseling With Electronic Decision Aids

Studies have shown that provider recommendations have a significant and positive impact on patient initiation and selection of a contraceptive method [38-40]. However, the provision of generic contraceptive information alone is insufficient. Prior literature highlights the importance of individualized contraceptive counseling [41-43] via a shared decision-making process [44-47], defined as an interactive process through which providers and patients communicate and arrive at a mutually agreeable decision [48]. Decisions aids are clinical tools designed to support patient-centered communication via shared decision making rather than provide paternalistic or generic information [41,49]. Prior contraceptive decision aids have been developed for use on electronic tablet or computer-based platforms across multiple geographic regions, practice settings, and patient populations and have been associated with improved patient involvement [50], decreased decisional conflict, increased patient knowledge [51], and increased contraceptive use [45,52]. Patients have reported numerous advantages to a Web-based platform over paper, including the interactive nature of the interface and the ability to compare contraceptive methods using filters and sorting options [53,54]. Furthermore, patients appreciated the use of a decision tool before a clinical visit to help them narrow down their contraception options and prepare questions for their providers [53].

### Rationale for Mixed Methods Study Design

The underlying rationale for collecting, integrating, and analyzing both qualitative and quantitative data are multifold: (1) quantitative data collected from self-administered survey items will provide descriptive statistics to allow for comparison with other practice settings and populations, (2) qualitative interviews will provide a deeper understanding of the lived experiences of women with chronic conditions and their primary care teams with respect to receiving and providing contraceptive services, respectively, (3) qualitative interviews provide an opportunity to immediately expand upon close-ended quantitative survey items that warrant further investigation [55], (4) leveraging the complementary nature of quantitative data and qualitative data maximizes our capacity to assess a broader range of theoretical constructs and contextual factors than if quantitative or quantitative methods were used alone [56], (5) collecting data via multiple methods (observations, interviews, surveys) improves the robustness and credibility of our findings [57].

### The Use of Theory and Implementation Science to Develop a Patient-Centered Intervention for Use in Usual Care Settings

To ensure the development of a patient-centered tool that explicitly upholds patient autonomy in decision making, we created a conceptual model that draws upon principles from reproductive justice theory and health behavior theories. This conceptual model will provide a preliminary prototype for the decision tool, which will be modified iteratively during this study phase. To develop an intervention that is contextualized for use in real-world clinical practices, our study design is informed by implementation science, an emerging field of methods and approaches that address the challenges of implementing health interventions in usual practice settings.[58] We use selected constructs from 2 frameworks commonly used in implementation science: the Consolidated Framework for Implementation Research (CFIR) [59] and the Theoretical Domains Framework, to guide data collection and analysis on the practice and provider level, respectively.

The overall goal of this mixed methods implementation project, the *MiHealth MiChoice study*, is to design and implement a theory-driven, Web-based contraceptive decision tool that can be accessed on an electronic tablet or computer before a clinical visit by women with chronic conditions who are seen in primary care settings. The feature of this tool that sets it apart from prior decision aids is that it will be tailored to factor in the personal preferences and medical history of a specific individual in a manner that also reflects evidence-based guidelines. The development and testing of this tool will occur over 3 phases (a predevelopment, development, and testing phase). The aim of this study protocol for phase 1 is to identify multilevel contextual factors that should drive the design and implementation of the contraceptive decision tool and explain subsequent study outcomes [60].

## Methods

### Overall Study Design

This mixed methods implementation study consists of 3 phases. This protocol focuses on phase 1, which is to identify the most critical patient-, provider-and practice-level factors that should inform the design and implementation of the decision-support tool. In phase 2, we will work with an expert health informatics team and an advisory council comprising patients, providers, and decision aid experts to build the Web-based decision tool that is accessible via a secured weblink from a computer or handheld tablet. Findings from phase 1 and a novel conceptual model (described in Figure 1 below) will inform iterative prototypes of the decision tool. In phase 3, the decision tool will be compared with usual care in a randomized controlled trial. We have received ethics approval for this study protocol by the University of Michigan Institutional Review Board (HUM00128060).

**Figure 1 figure1:**
[figure not shown]
Multiphase mixed methods design. PCP: primary care provider; RCT: randomized controlled trial; CC: chronic condition.

### Phase 1 Study Design

This is a convergent mixed methods design phase that focuses primarily on qualitative data collection and analysis with concurrent quantitative data collection and analysis. We will conduct semistructured, qualitative interviews of patients, PCPs, and practice staff members. All study participants will complete quantitative written surveys or electronic surveys via Qualtrics (Qualtrics, Provo, UT) before their qualitative interviews. The quantitative survey items complement the qualitative interview guide with the goal of obtaining maximal depth and breadth of understanding of each construct. Semistructured field observations in practices and collection of practice artifacts (eg, clinical protocols and patient intake forms) will further diversify our data sources and optimize data triangulation, which in turn will reduce the risk of systematic biases based on reported behaviors and experiences alone [61].

### Sampling Strategy, Eligibility, and Recruitment

#### Practices

To balance similarity and variation across practices, providers, and patients, we will use a combination of purposeful sampling techniques as described by Palinkas and colleagues [62]. Eligible practices include practices that identify as family medicine, internal medicine, internal medicine-pediatric, or any combination of these. First, we will use criterion sampling to select individuals who have experiences that are relevant to the phenomenon of interest [62]; for this study, we aim to select practices for which a contraceptive intervention is both clinically relevant and feasible to implement. Because LARC methods (intrauterine device and implant) are the most effective reversible methods and medically appropriate for the vast majority of women with chronic conditions [36,37,63], we will recruit practices that either provide LARC or assist with referrals for LARC. Therefore, eligible practices must have: (1) one or more providers who currently offer prescription contraception (eg, oral contraceptive pills), and (2) informal or formal processes to refer patients who desire LARC methods to another site *or* provide LARC methods on site. To achieve maximum variation in practice attributes that are associated with variations in contraceptive practice [31,64], clinical sites will be sampled to reflect a range of location (urban, suburban, and rural practices), a balance between private practices and practices with federal designations (federally qualified health centers, rural health center, medically underserved areas), and diversity in the racial/ethnic background of patients. Thus, maximum variation sampling aims to achieve breadth in sampling and can highlight differences between practices. To complement this approach, we will also use snowball sampling such that participating practices suggest other practices for recruitment; this approach tends to select practices that share characteristics and thus will help to achieve depth of understanding of similar practices [62]. We will recruit practices through The Great Lakes Research Into Practice Network, a statewide practice-based research network that is recognized by the Agency for Healthcare Research and Quality [65].

#### Sample Size

To achieve the depth and variation in practices as described above, we aim to enroll 6 clinical sites. For individual qualitative interviews, prior literature has documented that 6 to 12 interviews per homogeneous group provide sufficient qualitative data to reach saturation, the point at which analysis produces no new information, or disconfirming or confirming evidence [55,66]. On the basis of the sampling strategy described, we aim to enroll 30 patients, 30 PCPs, and 30 staff members (nurses, medical assistants, and administrative staff). Our definitions of homogenous groups are summarized below and in Multimedia Appendix 1. Purposeful sampling will be driven by this matrix such that the perspectives of individuals in each category are represented in qualitative interview data with the goal of data saturation. We expect this category to evolve based upon patient population characteristics in recruited practices.

#### Practice Members (Primary Care Practices and Staff)

Eligible practice members must be aged 18 years or older, English-speaking, able to give informed consent, and be indirectly or directly involved with patient care. PCPs must be physicians, nurse practitioners, physician assistants, or certified nurse midwives, who currently provide preventive health and management of chronic conditions to reproductive-aged women [62]. To complement criterion sampling as described above, we seek maximal variation [62] in PCPs’ contraceptive practices and will sample individuals who: (1) do not provide prescription contraception (eg, oral contraceptive pills), (2) provide prescription contraception but *do not* insert LARC devices, or (3) provide prescription contraception *and* insert LARC devices. For practice staff members other than PCPs, we aim to gather staff perspectives regarding contraceptive services and interventions that may differ based upon their primary responsibilities and context of patient interaction: (1) director or manager (clinical director, administrative director, nurse manager), (2) work with PCPs during clinical visits (nurses, medical assistants, licensed practical nurses), and (3) other services (social work, complex care management, pharmacist, behavioral counselor). A designated practice liaison (eg, medical director, office manager) will assist the study team to identify eligible practice members and extend invitations for study participation.

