### Data Analysis

All interview audiotapes will be transcribed verbatim. Qualitative analysis is an iterative process during which investigators go through cycles of reading, summarizing, and re-reading data [83,84]. The qualitative team is composed of 4 individuals from different professional backgrounds and research disciplines, including family medicine, dentistry, epidemiology, and health behavior. Though all team members identify as female, they vary in age, sexual orientation, religious background, and race/ethnicity. The interview transcripts will be uploaded and organized using MAXQDA software (VERBI GmbH, Berlin, Germany Version 12.3.1). We will conduct analysis through a series of iterative steps adapted from techniques described by Marshall and Rossman [85]. First, each team member will review several transcripts independently and code the content of each transcript. Because our research design is driven by predetermined theoretical constructs and research aims, our initial coding will be done with a theory-generated code template [86]. In vivo coding will also occur as new themes emerge from the interviews [85]. The team members will discuss, compare, and reconcile differences in coding and create a consensus code template, which will then be used to code the remainder of transcripts. Analysis of semistructured observations and practice artifacts proceeds in similar manner as described for interview transcripts. Themes and patterns will be identified and synthesized, using the preidentified theoretical constructs as a guide (Multimedia Appendices 2-4), as well as new codes and themes as they emerge. To increase the trustworthiness of our qualitative findings, we will triangulate our qualitative findings on multiple levels [54]: (1) methodological triangulation, by comparing and integrating with quantitative survey data, (2) data triangulation, by comparing and contrasting data obtained via interviews, surveys, observations, and artifacts, and (3) theoretical triangulation, by gathering multiple perspectives of the same phenomenon (patient-, provider-, practice-level perspectives). Data collection continues until saturation is reached, or until we no longer identify new or disconfirming or confirming data [84] with respect to the original research aim. Quantitative survey data will be summarized with simple descriptive statistics (frequencies, means, and SDs). We will conduct bivariate analyses with Fisher exact test to explore the following relationships: (1) demographic traits of providers and their contraceptive recommendations and practices, (2) practice attributes and providers’ contraceptive recommendations and practices, (3) the presence of different chronic conditions and current pregnancy desires among women, and (4) the presence of different chronic conditions and current contraceptive use among women. As described by Fetters [60], we will merge the quantitative and qualitative strands of data by identifying content from both datasets to compare, contrast, and synthesize. A final interpretation will summarize to what extent and how the results from the qualitative and quantitative data contribute to the identification of patient-, provider-, and practice-level factors that will then shape the design and implementation of the decision tool.

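### The mix of PCP contraceptive practices is set by recruitment, so it should not be tested against practice attributes in the interview sample or offered for comparison with other settings

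*Protocol article*

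**What the plan says.** Under *Practice Members (Primary Care Practices and Staff)*, PCPs are sampled on their own contraceptive practice: "we seek maximal variation [62] in PCPs’ contraceptive practices and will sample individuals who" fall into one of three categories (no prescription contraception; prescription without LARC insertion; prescription with LARC insertion). A liaison in each practice helps to identify and invite them.

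Under *Practices*, sites are chosen on related variables: "To achieve maximum variation in practice attributes that are associated with variations in contraceptive practice", they are spread over location, private or federally designated status, and the racial and ethnic background of patients. Each site must also have "one or more providers who currently offer prescription contraception (eg, oral contraceptive pills"), and must either provide LARC or refer for it.

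Under *Sample Size*, "we aim to enroll 30 patients, 30 PCPs, and 30 staff members" from 6 sites. Each category in the sampling matrix is to be represented. The text shown gives no number per category or per site for PCPs.

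Under *Data Analysis*, "We will conduct bivariate analyses with Fisher exact test to explore the following relationships". Relationship (1) is "demographic traits of providers and their contraceptive recommendations and practices". Relationship (2) sets practice attributes against the same provider outcomes.

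Under *Rationale for Mixed Methods Study Design*, one stated purpose of the survey descriptives is comparison with other practice settings and populations.

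**The concern.** A variable used to choose PCPs is then analysed as something observed about them. This has two consequences.

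First, the proportions of PCPs who do not prescribe, who prescribe only, and who also insert LARC reflect how the categories were filled. They do not estimate the mix in these practices or anywhere else, so they cannot serve the stated comparison with other settings.

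Second, in relationship (2) both sides of the table are purposively chosen: sites on attributes linked to contraceptive practice, and PCPs on contraceptive practice itself. How many PCPs of each category come from each site depends on an unstated fill rule and on whom the liaison invites. A null or a positive result can come from that rule. The quantitative results feed into naming the practice-level factors that shape the decision tool, and the article attaches no caution to this comparison.

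**Working it through.** **Inputs from the protocol article.** 30 PCPs, 6 sites, three PCP categories, 6 to 12 interviews per homogeneous group. Hence 30/6 = 5 PCPs per site on average. Three categories need 3 × 6 = 18 to 3 × 12 = 36 interviews, so 30 (10 per category if equal) is compatible with the saturation argument. There is no power calculation or significance level to reproduce.

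**Assumptions, not in the document.** Two-sided Fisher test at 0.05; 20% of PCPs insert LARC; a binary provider trait with 50% prevalence; true odds ratio 1 or 5; a sample of 10 inserters and 20 non-inserters; 3 sites with and 3 without a practice attribute; 8,000 simulated samples per scenario; no clustering within sites.

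**Step 1: the margin.** The sample share of inserters is 10/30 = 33%, against 20% in the assumed population. In odds this is (10/20)/(20/80) = 0.50/0.25 = 2, so inserters are over-represented two to one by design.

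**Step 2: relationship (1), selection on practice only.** Let f1 and f0 be the sampling fractions of inserters and non-inserters, and a, b, c, d the population cells (inserters and non-inserters with the trait, then without it). The expected sample odds ratio is (a·f1 × d·f0)/(b·f0 × c·f1) = ad/(bc). The fractions cancel, as in a case-control study. They do not cancel in risks or risk differences.

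| | Random sampling | Sampling on practice |
|---|---|---|
| Rejection, true odds ratio 1 | 2.4% | 2.7% |
| Rejection, true odds ratio 5 | 23% | 36% |
| Median odds ratio, true value 5 | 4.30 | 4.31 |
| Mean risk difference, true value 0.23 | 0.23 | 0.33 |

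Both median odds ratios lie below 5, with 0.5 added to each cell and only 30 PCPs. The sampling scheme makes no difference to them.

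**Step 3: relationship (2), three possible fill rules.** Assume true insertion rates of 50% and 10% by practice attribute: odds ratio (0.5/0.5)/(0.1/0.9) = 9.0.

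| Fill rule | Mean difference | Rejection |
|---|---|---|
| No quota | 0.40 | 53% |
| Quota over the whole sample only | 0.44 | 62% |
| Balanced within each site (1 or 2 inserters of 5) | 0.00 | 0% |

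Under the balanced rule each group of 15 PCPs holds 3 to 6 inserters. The most extreme table, 6/15 v 3/15, has p = 0.427, so rejection is impossible whatever the truth.

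**Step 4: joint selection.** If the sampling fractions depend on the attribute as well, the odds ratio is multiplied by (f11 × f00)/(f10 × f01), where the first index is practice and the second the attribute. With no true association and a multiplier of 2, 3 or 5, the median odds ratio is 1.9, 2.8 or 4.3 and rejection is 8%, 18% or 35%.

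**The case against.** A reader might infer that every Fisher result on contraceptive practices, in both relationships, is dictated by the sampling. The documents do not support that, and several points on the other side stand.

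- No section samples PCPs on demographic traits. Relationship (1) is therefore selection on the outcome alone, and Step 2 shows that the test and odds ratio survive.
- Equal thirds within each practice are not in the text. *Sample Size* asks only that categories be represented. Approximately equal numbers are sought for patients, not PCPs. Thirds of about 5 PCPs per site are not possible exactly, and a site that only refers for LARC would ordinarily have no inserter to recruit.
- Filling categories from wherever candidates exist does not by itself create an association: the whole-sample quota in Step 3 keeps it. A false one needs invitation to depend on attribute and category together, which the text neither states nor excludes.
- A reader might also call on-site LARC a circular attribute. *Data Analysis* does not list it as a tested attribute; under *Practices* it appears only in an eligibility condition.
- The outcome includes contraceptive recommendations, on which nobody is sampled.
- The tests explore, the phase is mainly qualitative, and no rule keeps or drops a factor on a p-value.

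The sampling matrix (Multimedia Appendix 1) is not shown and may settle the fill rule. None of this makes the category frequencies population values. Nor does it protect relationship (2) as the article states it.

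**Conclusion.** The concern holds in limited form. The distribution of PCPs over the three categories is set by recruitment and is unsuitable for comparison with other settings; in the assumed example, 33% stands for a true 20%. Relationship (2), as far as it concerns contraceptive practices, depends on an unstated fill rule. Under the assumed rates, a true difference of 0.40 becomes 0.00 if categories are balanced within sites, while joint selection raises false rejection to between 8% and 35%. These sizes rest on the assumptions listed and show what could happen, not what will.

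Relationship (1) is not invalid. If selection ignores provider traits, its Fisher test and odds ratio can be used, but its risks and risk differences cannot.

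This is worth correcting but is not essential, because the tests are exploratory and secondary to the qualitative work.

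**What to change.** In *Data Analysis*:

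1. Relationship (2): do not test the three-category sampling variable in the interview sample. Add one question to the existing Practice Information Form asking how many of the practice's PCPs fall in each category. Present that mix descriptively across the 6 sites. Keep contraceptive recommendations as the surveyed outcome.
2. Relationship (1): keep the comparison, report odds ratios rather than risks or risk differences, and state that the category totals are set by design.

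In *Rationale for Mixed Methods Study Design*: exclude the PCP category frequencies from the descriptives offered for comparison with other settings.

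The cost is one extra question for the practice liaison (the form has 29 items) and fewer reported tests. Recruitment and the qualitative work do not change. Splitting the 30 PCPs by category to compare recommendations within each is not needed: it would leave about 10 per category and very little information.
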